## **Randomization and blinding**

The randomization sequence will be generated by software available online at [www.randomizer.org](http://www.randomizer.org) by a study collaborator not involved in the processes of collecting or evaluating the results. The software will generate a sequence of uniformly random numbers for 2 groups. The sequence generated by the program will be placed in opaque envelopes and numbered sequentially. The opaque and sealed envelopes will only be under the domain of the researcher responsible for the randomization. Only the collaborators in charge of administering the intervention protocol will be aware of each participant's allocation group. Furthermore, all

outcome assessors will remain blinded during the study to participant allocation.

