### Cardiac morphology and function analysis

#### Cardiac morphology

Cardiac nuclear magnetic resonance (NMR) can be used for several important evaluations after acute myocardial infarction. MRI allows the diagnosis of myocardial infarction in its acute or chronic condition, provides several prognostic indicators that can impact the risk stratification of patients, in addition to allowing the identification of complications after AMI, such as aneurysm, pericarditis, and thrombi among others (53). The evaluation of the extent of scarring after AMI is a valuable predictor of therapeutic success, being used as a common endpoint in clinical trials. The extent of infarction is inversely related to clinical prognosis and is a more sensitive predictor than mass and ventricular ejection fraction of ventricular tachycardia, ultimately predicting all-cause mortality and ejection fraction-independent survival (53).

In this study, standard protocols will be used to assess cardiac morphology and function, such as end-systolic and diastolic volumes and ventricular ejection fraction evaluated through the CINE SSFP sequence, in addition to the delayed enhancement sequence with gadolinium (53). The exam will be performed at baseline, still during hospital stay, around the fourth to sixth day after the AMI and in two follow-up moments, the first one from 4 weeks after the event, with a tolerance of up to 2 weeks for image and the second from 3 months after the event with a tolerance of two weeks.

The technique used to evaluate the scar extension will be the delayed enhancement with the administration of gadolinium chelate. The patient will receive the gadolinium chelate between 10 and 20 minutes before the exam. In the presence of scar tissue, there is an increase in the extracellular space in relation to the intracellular environment due to the rupture of the cardiomyocyte membranes, with greater gadolinium impregnation in this region, generating hyper-enhancement in the image (53). Scar size assessment will use the following semi-quantitative method: Visual scoring of 17 standardized areas, on a 5-point scale, where 0= no hyperenhancing, 1= 1-25%, 2= 26 – 50%, 3=51

– 75% and 4= 76 – 100% hyperenhancing. The total scar score is given by adding the

scores for each segment and dividing by 17 (53).

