## **Statistic Strategy**

The variables of interest will be analyzed using the software (Graph Pad Prism version 7.0) and initially evaluated for the normal distribution of data using the Shapiro-Wilk test considering  $n < 30$ . In the case of data with normal distribution, they will be analyzed for the mean and standard deviation. Data without normal distribution will be analyzed for median and percentiles. Comparison analyses of the physical functional variables of the 30CST, MRI morphological variables, and HRV cardiac functional variables of the PRE-CR and POST-CR times of each group will be performed using the Wilcoxon test if the data were non-parametric and the paired t-test if the data were parametric. Comparison between the control and intervention groups for CPET will be performed using the independent t-test or the Mann-Whitney test, depending on the normality of the data. The reliability and validity of the 30CST will be analyzed using Spearman's correlation and the intra-examiner reliability coefficient. For all hypothesis tests, a significance of 5% probability ( $P < 0.05$ ) of error will be assigned.

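### No masking of MRI readers to scan date or order is specified, although the visual scar score is tested only before versus after rehabilitation within each group

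*Protocol*

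**What the plan says.** **Masking.** Protocol, Randomization and blinding, states that all "outcome assessors will remain blinded during the study to participant allocation". MRI readers are not named separately. Neither that section nor Cardiac morphology mentions scan date, scan order or access to a patient's earlier scans.

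**Measurement.** Protocol, Cardiac morphology, defines scar size by "Visual scoring of 17 standardized areas, on a 5-point scale": grades 0 to 4, summed and divided by 17. The other MRI measures are "end-systolic and diastolic volumes and ventricular ejection fraction evaluated through the CINE SSFP sequence". On timing, "The exam will be performed at baseline, still during hospital stay, around the fourth to sixth day after the AMI and in two follow-up moments", from 4 weeks and from 3 months after the event.

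**Analysis.** Protocol, Statistic Strategy, compares "MRI morphological variables, and HRV cardiac functional variables of the PRE-CR and POST-CR times of each group", using "the Wilcoxon test if the data were non-parametric and the paired t-test if the data were parametric". The only between-group test it names is for the exercise test: "Comparison between the control and intervention groups for CPET will be performed using the independent t-test".

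**Aim.** The MRI objective, listed under Secondary objectives, is to observe the influence of early rehabilitation on ventricular remodelling. The Study Design section states a superiority hypothesis.

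**The concern.** Masking to arm protects a comparison between arms. The comparison written for MRI runs along time, from early scan to late scan within one group. For that contrast, what matters is whether the reader knows which scan came first, and the protocol does not say.

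The scar score depends on a reader's judgement, and the Abstract expects a positive effect on cardiac structure and function. A reader who expects recovery and knows the order of the scans may grade the later one a little lower. That moves the tested quantity in one direction with no true change in the patient. It can happen in either group, because it does not depend on knowing the arm. A significant fall in scar score in the intervention group could then be reported as an effect of rehabilitation.

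**Working it through.** The protocol gives no planned effect, SD or reader-agreement figure for the scar score, so there is no stated figure to reproduce. The sample size was set for oxygen consumption, not MRI. What follows is an illustration, and its shifts and SDs are assumptions.

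**Inputs from the protocol**
- 17 segments, total divided by 17 (Cardiac morphology).
- 12 patients per group and a 30% allowance for losses (Sampling and Recruitment). 12 × 0.7 = 8.4, so about 8 per group may remain.
- Significance level 5% (Statistic Strategy). Sidedness is not stated; two-sided is assumed.

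**Assumptions**
- No true change in scar.
- On average, the later scan is graded one grade lower in k segments, with k = 1 or 2.
- The SD of the paired differences is 0.1, 0.2 or 0.3, and the differences are normal.

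**Step 1: shift in the score.** Shift = k/17. For k = 1 it is 1/17 = 0.059; for k = 2 it is 2/17 = 0.118.

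**Step 2: chance of a falsely significant paired t-test in one group.** The test statistic follows a noncentral t distribution with n − 1 degrees of freedom and noncentrality (shift/SD) × √n. The two-sided 5% critical values are 2.201 for n = 12 and 2.365 for n = 8. For example, with k = 2, SD 0.2 and n = 12, the noncentrality is (0.118/0.2) × √12 = 2.04 and the probability is 46%.

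| Shift | n | SD 0.1 | SD 0.2 | SD 0.3 |
|---|---|---|---|---|
| 0.059 (one segment) | 12 | 46% | 15% | 10% |
| 0.118 (two segments) | 12 | 96% | 46% | 24% |
| 0.059 (one segment) | 8 | 30% | 11% | 8% |
| 0.118 (two segments) | 8 | 81% | 30% | 16% |

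The nominal rate is 5%.

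**Step 3: the same question in SD units.** Let a shift of 0.5 SD of the paired difference fall on both groups. The chance of a significant result in the favourable direction in the intervention group is 35% with 12 patients and 23% with 8, against 2.5% with no shift. The chance that only the intervention group is significant in that direction is 0.353 × (1 − 0.353) = 23% with 12 per group, and 0.231 × (1 − 0.231) = 18% with 8.

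**Step 4: a between-group test under the same shift.** In 100,000 simulated trials per setting, with shifts of 0, 0.5 and 1.0 SD common to both groups and no treatment effect, an independent t-test on change was significant in 4.9% to 5.1%, for both 12 and 8 per group. The common shift cancels.

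**The case against.** **Silence is not evidence of unmasked reading.** A reader might infer that the MRI readers will see scan dates. The protocol does not say so. Reading conditions may be set in an imaging manual that is not shown. This stands, and the point is limited to masking that is not specified.

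**Remodelling is wider than scar.** A reader might infer that all remodelling results are equally exposed. The introduction describes remodelling as change in the geometry, mass and function of the ventricle. Volumes and ejection fraction come from the cine sequence and are not visual grades. This also stands: the concern is with the scar score.

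**The larger defect is the within-group analysis.** Even with perfect masking, a before-after test in one group cannot separate an effect of rehabilitation from natural recovery. With a between-group comparison, a reading shift common to both groups would do little harm. This stands and shapes the fix. It does not dispose of the point, because the analysis as written is the one that makes scan order matter.

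**Masking may fail at the contrast that matters.** The protocol itself says that MRI can distinguish acute from chronic infarction, so a scan at day 4 to 6 may be recognisable without its date. This stands as a limit on the benefit.

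**The error rates rest on assumptions.** They do, which is why they span 8% to 96%. The calculation also ignores that a segment graded 0 cannot go lower, which matters in low-risk patients with an ejection fraction above 50%. It uses the t-test although Wilcoxon is planned for non-normal data.

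**Conclusion.** The point holds as a minor one. The stated masking does not protect the contrast that the protocol plans to test for the scar score, and a systematic tendency to grade later scans lower would pass straight into that test. If such a tendency existed at the assumed sizes, false significance in one group would run from about 10% to 96% with 12 patients and from 8% to 81% with 8. These figures show sensitivity only; they do not forecast the trial's error rate.

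A reader might go further and conclude that a favourable MRI finding would be an artefact of reading. The documents do not support that: they give no sign that readers know the order, no size for any bias and no reader-agreement data. Nor would masked reading alone rescue the MRI objective, since the within-group analysis would still be unable to show an effect of rehabilitation. The low severity reflects that MRI serves one of six secondary objectives and that scar is one of several MRI variables.

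**What to change.** 1. **Cardiac morphology.** Add a sentence: each patient's scans are stripped of date, time point and arm, and are scored for scar in random order by the planned reader or readers once that patient's last scan is available. Reading volumes and ejection fraction in the same way is a low-cost extension.

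2. **Statistic Strategy.** Compare MRI change between groups at a named follow-up scan, for example the follow-up score adjusted for baseline. A reading shift common to both groups then cancels, and the objective on the influence of early rehabilitation can be addressed.

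**Cost.** Two short text changes, plus anonymising and shuffling at most 24 × 3 = 72 scans. No extra reader, scan or patient visit is needed. Research scoring has to wait for each patient's last scan. An acute scan may still be recognisable, so the first change reduces the bias but may not remove it. The second covers what remains, to the extent that it is common to both groups.

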### *Heart Rate Variability – HRV*

Heart rate variability (HRV) is an easy and non-invasive method to assess the integrity and functioning of the autonomic nervous system on heart rhythm. HRV can be observed by R-R intervals and its reduction is usually related to aging and worse health conditions (42,44,45).

In this research, the HRV will be measured before the randomization of the groups and at the outpatient return 30 days after hospital discharge using a Polar chest strap type heart rate monitor, model H10. The data provided by the heart rate monitor will be analyzed using Kubios HRV software. Variables of interest include those in the time domain: SDNN - standard deviation of all normal RR intervals recorded in a time interval, expressed in ms; pNN50 - represents the percentage of adjacent RR intervals with a duration difference greater than 50 ms. In addition to these variables, those in the frequency domain will be analyzed: High frequency component (HF) ranging from 0.15 to 0.4 Hz; Low frequency (LF) component, ranging from 0.04 to 0.15 Hz and the LF/HF ratio (45).

### Analysis of aerobic exercise dose in cardiac rehabilitation

Despite the standardized goal for aerobic exercise dose, each patient will have an individual tolerance limit for the progression of exercise dose, because of this, each patient will have their exercise dose monitored each CR week. The calculation method for aerobic exercise dose will be performed by multiplying the value of the estimated training intensity in (MET-task metabolic rate) estimated by the borg, the session time, and the frequency of sessions during each week, determining the dose in METxmin-Week (48).

### Cardiohemodinamic safety of early cardiac rehabilitation

The safety of the institutional protocol tested in this trial will occur through notifications

of adverse events during and after the CR sessions provided to patients in the intervention group. We will report adverse events session by session, listing the main ones: arrhythmias, chest pain, borg>13, drop in systolic blood pressure (SBP) above 10 mmHg, and cardiorespiratory arrest. Other events not previously listed will also be recorded in the patient follow-up and evaluation form as per Appendix A.

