In step 2, patients will follow early exercise-based cardiac rehabilitation performed following all prescription parameters (FITT-VP) and safety criteria recommended by ACSM, 2018 (33). The institutional protocol (**Appendix B**) will be performed with a **frequency** of 2 sessions per day, during the entire hospitalization, with an average of 8 to 10 total sessions; Low **intensity** for aerobic training with METs estimated by the subjective perception of effort of BORG between 9 to 12 reaching between 2 to 3 METs and for resistance training with 2 to 3 series of 60% of the maximum repetitions reached in the 30s sit-to-stand test; **Type** of exercises involved will be aerobic training using the cycle ergometer associated with resistance training using the body's own weight with functional sit-to-stand training; Aerobic training **time** ranging from 3 to 20 minutes. The **Volume or Dose** of aerobic training will be measured by calculating the training dose per session and the total dose applied during hospitalization, providing a value in time x intensity (METs) x frequency of accumulated sessions and total number of sessions x time. The structured **progression** in the protocol focuses on the time of aerobic exercise and the number of series of resistance training. The exercise sessions will follow the protocol presented, however, present individualized prescriptions based on tolerance time during aerobic training with a cycle ergometer and resistance training from the maximum number of repetitions reached in the 30s TSL evaluated

individually before randomization.

Before hospital discharge, patients in the intervention group will receive an exercise guidance booklet (Appendix C) to perform step 3 of semi-supervised and continued cardiac rehabilitation with the exercise time reached at the end of in-hospital rehabilitation, frequency of 5 x per week and progression of 5 minutes each week within the first month after hospital discharge, according to tolerance and self-monitoring of intensity through perceived exertion using the Borg scale, maintained between 9 to 12, to ensure light exercise to moderate intensity. In this phase, patients in the intervention group will be monitored weekly by telephone and will receive a diary (Appendix C) to record the time of daily and weekly activity that they must deliver when investigating when they return for reassessment 30 days after hospital discharge.

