All patients will be monitored before, during, and after each supervised care session with a frequency meter and pulse oximeter (Model Nonin Onyx 9500, Nonin Medical, USA and Polar H10), which will allow the assessment of heart rate and O2 saturation. Blood pressure will be evaluated before and after the session and during the ICU stay the electrocardiogram will be monitored throughout the exercise. Patients will be instructed to interrupt the exercise in case of malaise (dyspnea, excessive sweating, cyanosis, use of accessory muscles, vertigo, retching), chest pain, or borg greater than 13 for both dyspnea and muscle fatigue.

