**PHYSICAL EXAMINATION PER SESSION**

**Session 1:** Session start: HR:\_\_\_\_\_bpm RF:\_\_\_\_\_bpm SpO2:\_\_\_\_\_ % BP:\_\_\_\_\_mmHg  
End of session: HR:\_\_\_\_\_bpm RF:\_\_\_\_\_bpm SpO2:\_\_\_\_\_ % BP:\_\_\_\_\_mmHg  
Security: ☐ Angina ☐ Arrhythmia \_\_\_\_\_ ☐ Borg>=13 ☐ Fall of SBP>=10mmHg  
☐ CPA ☐ Others:\_\_\_\_\_ Vasoactive drug (Dose) ☐ \_\_\_\_\_ Devices:\_\_\_\_\_  
\_\_CR summary:\_\_\_\_\_

**Session 2:** Session start: HR:\_\_\_\_\_bpm RF:\_\_\_\_\_bpm SpO2:\_\_\_\_\_ % BP:\_\_\_\_\_mmHg  
End of session: HR:\_\_\_\_\_bpm RF:\_\_\_\_\_bpm SpO2:\_\_\_\_\_ % BP:\_\_\_\_\_mmHg  
Security: ☐ Angina ☐ Arrhythmia \_\_\_\_\_ ☐ Borg>=13 ☐ Fall of SBP >=10mmHg  
☐ CPA ☐ Others:\_\_\_\_\_ Vasoactive drug (Dose) ☐ \_\_\_\_\_ Devices:\_\_\_\_\_  
\_\_CR summary:\_\_\_\_\_

**Session 3:** Session start: HR:\_\_\_\_\_bpm RF:\_\_\_\_\_bpm SpO2:\_\_\_\_\_ % BP:\_\_\_\_\_mmHg  
End of session: HR:\_\_\_\_\_bpm RF:\_\_\_\_\_bpm SpO2:\_\_\_\_\_ % BP:\_\_\_\_\_mmHg  
Security: ☐ Angina ☐ Arrhythmia \_\_\_\_\_ ☐ Borg>=13 ☐ Fall of SBP >=10mmHg  
☐ CPA ☐ Others:\_\_\_\_\_ Vasoactive drug (Dose) ☐ \_\_\_\_\_ Devices:\_\_\_\_\_  
\_\_CR summary:\_\_\_\_\_

**Session 4:** Session start: HR:\_\_\_\_\_bpm RF:\_\_\_\_\_bpm SpO2:\_\_\_\_\_ % BP:\_\_\_\_\_mmHg  
End of session: HR:\_\_\_\_\_bpm RF:\_\_\_\_\_bpm SpO2:\_\_\_\_\_ % BP:\_\_\_\_\_mmHg  
Security: ☐ Angina ☐ Arrhythmia \_\_\_\_\_ ☐ Borg>=13 ☐ Fall of SBP >=10mmHg  
☐ CPA ☐ Others:\_\_\_\_\_ Vasoactive drug (Dose) ☐ \_\_\_\_\_ Devices:\_\_\_\_\_  
\_\_CR summary:\_\_\_\_\_

**Session 5:** Session start: HR:\_\_\_\_\_bpm RF:\_\_\_\_\_bpm SpO2:\_\_\_\_\_ % BP:\_\_\_\_\_mmHg  
End of session: HR:\_\_\_\_\_bpm RF:\_\_\_\_\_bpm SpO2:\_\_\_\_\_ % BP:\_\_\_\_\_mmHg  
Security: ☐ Angina ☐ Arrhythmia \_\_\_\_\_ ☐ Borg>=13 ☐ Fall of SBP >=10mmHg  
☐ CPA ☐ Others:\_\_\_\_\_ Vasoactive drug (Dose) ☐ \_\_\_\_\_ Devices:\_\_\_\_\_  
\_\_CR summary:\_\_\_\_\_

**Session 6:** Session start: HR:\_\_\_\_\_bpm RF:\_\_\_\_\_bpm SpO2:\_\_\_\_\_ % BP:\_\_\_\_\_mmHg  
End of session: HR:\_\_\_\_\_bpm RF:\_\_\_\_\_bpm SpO2:\_\_\_\_\_ % BP:\_\_\_\_\_mmHg  
Security: ☐ Angina ☐ Arrhythmia \_\_\_\_\_ ☐ Borg>=13 ☐ Fall of SBP >=10mmHg  
☐ CPA ☐ Others:\_\_\_\_\_ Vasoactive drug (Dose) ☐ \_\_\_\_\_ Devices:\_\_\_\_\_  
\_\_CR summary:\_\_\_\_\_

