**Session 7:** Session start: HR:\_\_\_\_\_bpm RF:\_\_\_\_\_bpm SpO2:\_\_\_\_\_ % BP:\_\_\_\_\_mmHg  
End of session: HR:\_\_\_\_\_bpm RF:\_\_\_\_\_bpm SpO2:\_\_\_\_\_ % BP:\_\_\_\_\_mmHg  
Security: ☐ Angina ☐ Arrhythmia \_\_\_\_\_ ☐ Borg>=13 ☐ Fall of SBP >=10mmHg  
☐ CPA ☐ Others:\_\_\_\_\_ Vasoactive drug (Dose) ☐ \_\_\_\_\_ Devices:\_\_\_\_\_  
\_\_CR summary:\_\_\_\_\_

**Session 8:** Session start: HR:\_\_\_\_\_bpm RF:\_\_\_\_\_bpm SpO2:\_\_\_\_\_ % BP:\_\_\_\_\_mmHg  
End of session: HR:\_\_\_\_\_bpm RF:\_\_\_\_\_bpm SpO2:\_\_\_\_\_ % BP:\_\_\_\_\_mmHg  
Security: ☐ Angina ☐ Arrhythmia \_\_\_\_\_ ☐ Borg>=13 ☐ Fall of SBP >=10mmHg  
☐ CPA ☐ Others:\_\_\_\_\_ Vasoactive drug (Dose) ☐ \_\_\_\_\_ Devices:\_\_\_\_\_  
\_\_CR summary:\_\_\_\_\_

**Surplus sessions:** Any adverse events? Which? \_\_\_\_\_

| COMPLEMENTARY EXAMS                                                                                                                                                                                                                                              |                          |
|------------------------------------------------------------------------------------------------------------------------------------------------------------------------------------------------------------------------------------------------------------------|--------------------------|
| Electrocardiogram (1): _____
 Regular rhythm  Atrial fibrillation  Pacemaker  RBBB  LBBB  Others _____ | Date: ____ / ____ / ____ |
| Echocardiogram (1): EF _____ PAP _____ Others: _____                                                                                                                                                                                                      | Date: ____ / ____ / ____ |
| X-RAY (1): _____                                                                                                                                                                                                                                          | Date: ____ / ____ / ____ |

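### The session form ticks Borg 13 and a 10 mmHg systolic fall as safety events, but the protocol text counts only values above those limits

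*Protocol*

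**What the plan says.** The section on cardiohemodynamic safety says that adverse events in the intervention group will be reported for each session. Among the main ones it names "borg>13, drop in systolic blood pressure (SBP) above 10 mmHg". Both limits are strict. The monitoring paragraph of the early cardiac rehabilitation programme uses the same strict Borg limit as a reason to stop exercise: "borg greater than 13 for both dyspnea and muscle fatigue".

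The Appendix A form, under the physical examination per session, has safety boxes labelled "Borg>=13 ☐ Fall of SBP>=10mmHg" for Session 1. The same inclusive limits recur in every block through Session 8 (for example "Fall of SBP >=10mmHg"). Each block also has blanks for blood pressure at the start and end of the session, an entry for other events and a free-text summary line. It has no blank for the Borg rating itself.

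The secondary objectives include identifying the rate of adverse events and the safety level of the protocol.

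**The concern.** Two of the five events named in the safety section have one threshold in the text and another on the form where staff tick them. No sentence says that one overrides the other. The same sessions could then give two different rates, depending on whether the analyst counts ticks or applies the text. At Borg 13 the monitoring rule lets the patient continue, yet the form asks staff to record a safety event.

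The boundary values are plausible ones. The prescription is "METs estimated by the subjective perception of effort of BORG between 9 to 12", so 13 is the first value above target. It is one point above the 11 to 12 set for STEPS 5 to 8 in Appendix B and three points above the 9 to 10 set for STEPS 1 to 4. A fall of 10 mmHg is a round figure. At stake is whether the reported rate is the one that the safety section defines.

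**Working it through.** The protocol states no expected adverse event rate, so there is no figure to reproduce. The check is a comparison of the two definitions.

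| Session result | Event under the safety section | Ticked on the form |
|---|---|---|
| Borg 12 or less | no | no |
| Borg exactly 13 | no | yes |
| Borg 14 or more | yes | yes |
| Systolic fall below 10 mmHg | no | no |
| Systolic fall exactly 10 mmHg | no | yes |
| Systolic fall above 10 mmHg | yes | yes |

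The definitions differ only on the boundary, and always in the same direction. The form over-counts relative to the text, and its limits exclude no event that the text would count.

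**Is it an extraction fault?** No. The strict limits appear partly in words (above, greater than), and the inclusive sign stands on 2 items × 8 blocks = 16 labels.

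**Can the ticks be corrected afterwards?**
- Systolic pressure: yes, for Sessions 1 to 8. Pressure is taken before and after each session and both readings have a blank, so the fall can be recomputed and the strict limit applied.
- Borg: not reliably. A tick does not separate 13 from 14 or more, and the rating is available only if someone chose to write it in free text.

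**Size.** Let b be the number of sessions exactly on the boundary for an item and N the number of sessions recorded. Then

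form rate − text rate = b / N.

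For a rate of any event, b counts only boundary sessions with no other event. If b = 0, the rates are identical.

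The protocol gives 12 patients per group (Sampling and Recruitment) and, for sessions, "with an average of 8 to 10 total sessions". Assuming full attendance:
- 8 sessions each: N = 12 × 8 = 96, so one boundary session shifts the rate by 1/96 = 1.04 percentage points.
- 10 sessions each: N = 12 × 10 = 120, and 1/120 = 0.83 points.
- Counting only STEPS 4 to 8, which the intervention group alone receives: N = 12 × 5 = 60, and 1/60 = 1.67 points.

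These figures are only 1/N. They show what one such session would do, not that any will occur. Losses would make N smaller and the shift per session larger. The protocol gives no distribution of Borg ratings or pressure changes, so b cannot be derived. Purely as an assumed range, boundary shares of 1%, 5% and 10% of 96 to 120 sessions would be about 1, 5 to 6, and 10 to 12 sessions.

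**The case against.** The strongest reply is that this matters little. The rate is descriptive, comes from one arm, and the statistical section plans no test on it. The safety section is where the protocol says what will be reported, and the monitoring rule agrees with it on Borg, so the strict limits are the natural governing definition. A form more inclusive than the reporting rule loses no boundary case. The safety section also presents its list as the main events and allows others to be recorded on Appendix A, so the list is not closed. Borg has to be obtained anyway, because training intensity for the dose is "estimated by the borg, the session time, and the frequency of sessions during each week", and staff could write it on the summary line.

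Most of this stands and limits the weight of the point. It does not remove it. The allowance for other events most naturally means other kinds of event, not a second threshold for a listed one. If the safety section governs, the form's ticks still do not measure what it defines. The dose calculation does not guarantee that the highest rating of a session is kept, and nothing requires it to be written as free text.

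A reader might infer more than the documents support:
- *That the Borg data are lost for certain.* The block lacks a dedicated field, but free text may hold the value.
- *That sessions beyond the eighth are part of the contradiction.* Their line asks only "Any adverse events? Which". It states no conflicting threshold, so the safety section applies unchanged. The thin layout there is a separate matter.
- *That the trial's safety or efficacy conclusions are undermined.* The mismatch touches two descriptive items in the intervention group, and no efficacy comparison uses them.

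**Conclusion.** The contradiction is real: strict limits in the text, inclusive limits on the form, repeated in all eight session blocks. A count of ticks can overstate the adverse event rate as the safety section defines it. For systolic pressure the error can be corrected from the recorded readings in Sessions 1 to 8. For Borg it cannot be corrected reliably. The excess is b/N, with b unknown and possibly zero. The per-session shifts of 0.83 to 1.67 points rest on assumed full attendance by 12 patients and on the assumed session counts. The consequence is limited to a descriptive rate in one arm. Severity: minor, but worth correcting because the rate is a named objective and the correction is nearly free.

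**What to change.** In the Appendix A blocks for Sessions 1 to 8, change the two boxes to Borg >13 and systolic fall >10 mmHg, so that they match the safety section and, for Borg, the stopping rule. Add one blank per block for the highest Borg rating of the session. The text of the protocol body stays as it is.

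The cost is 16 relabelled boxes and 8 blanks. No new measurement is needed: blood pressure is already taken before and after each session, and Borg is already needed for the stopping rule and the dose.

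Keeping the inclusive boxes as a screening prompt would also be defensible, provided that the Borg value is recorded and one sentence says that the reported rate uses the strict limits. The same fields for sessions after the eighth, and separate ratings for dyspnea and muscle fatigue, are optional improvements and are not needed to remove the error.
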